## Abstract

**Background:**

Many women suffer from health problems after giving birth, which can lead to sick leave. About 30% of Dutch workers are on sick leave after maternity leave. Structural contact of supervisors with employees on maternity leave, supported by early medical advice of occupational physicians, may increase the chances of return-to-work after maternity leave. In addition, to understand the process of sick leave and return-to-work after childbirth it is important to gain insight into which factors hinder return-to-work after childbirth, as well, as which prognostic factors lead to the development of postpartum health complaints. In this paper, the design of the Mom@Work study is described.

**Methods:**

The Mom@Work study is simultaneously a randomised controlled trial and a cohort study. Pregnant women working for at least 12 hours a week at one of the 15 participating companies are eligible to participate. The supervisors of these pregnant employees are randomised at 35 weeks pregnancy into the intervention group or control group. During maternity leave, supervisors in the intervention group contact their employee six weeks after delivery using a structured interview. When employees do not expect to return to their jobs at the end of their scheduled maternity leave due to health problems, the supervisor offers early support of the occupational physician. Supervisors in the control group have no structural contact with their employees during maternity leave. Measurements take place at 30 weeks pregnancy and at 6, 12, 24 and 52 weeks postpartum. In addition, cost data are collected. For the RCT, primary outcome measures are sick leave and return-to-work, and secondary outcome measures are costs, health, satisfaction with intervention and global feelings of recovery. Outcome measures for the cohort are pregnancy-related pelvic girdle pain, fatigue and depression. Finally, a number of prognostic factors for return-to-work and for the development of complaints will be measured.

**Discussion:**

The Mom@Work study will provide important information about return-to-work of employees after giving birth. Results will give insight in prognosis of postpartum sick leave and complaints. Also, the role of supervisors and occupational physicians in successful return-to-work after childbirth will be clarified.

## Background

Many women experience health problems during the first year after childbirth [1-4]. Common postpartum problems are fatigue, bowel problems, lack of sleep, postpartum depression, urinary incontinence, back pain and pelvic pain [1,4-6]. These common physical and mental health problems can lead to sick leave and long-term sickness absence from work [1].

In The Netherlands, every pregnant employee has the right to receive paid maternity leave, also called pregnancy and delivery leave. The total duration of this leave is 16 weeks, divided over four to six weeks before the delivery term and 10–12 weeks thereafter. About 90% of Dutch working women had the intention to return-to-work (RTW) after the birth of their first child [7]. A Dutch study described that 29% of working women were absent due to sickness for two weeks or more after maternity leave [1]. Sick leave postpartum was often long-term; in 55% of cases the sickness absence exceeded 12 weeks. The most occurring causes of sick leave postpartum were: pelvic pain (30%), back pain (26%), fatigue (23%), and mental problems (14%). [1]. Despite an abundance of literature about regular RTW and sick leave, little is known about the process of RTW after childbirth. A broad range of factors may contribute to RTW or sick leave, for instance factors like breastfeeding, childcare, social support, work load, distress, health, lack of sleep or health complaints. Therefore, it is important to gain insight into which factors hinder RTW after the end of maternity leave, as well as into the prognostic factors which lead to the development of these complaints.

There are several possible explanations for this high sick leave and postponed RTW postpartum. The postpartum care for women is probably to fragmented. At six weeks postpartum, women have their last contact with the midwife or obstetrician, who have limited time and who give only little or no information about RTW. At Youth Health Care centres only the child's health is considered and due to limited time the mother's health is often neglected. If there are health problems, women consult their general practitioner just before the scheduled maternity leave ends. In addition, these women with postpartum health complaints may not receive timely medical attention of their occupational physician (OP), who is currently not involved until 12–18 weeks postpartum. This may be too late; health complaints may have existed for a considerable time, while early intervention after the onset of complaints seems to be important [8-11], because prognosis for RTW becomes worse due to long-term sick leave [12]. An accompanying problem is the lack of communication between these different medical health care providers. Furthermore, women are not supported in the way they should be by their OP after maternity leave[13]. Postpartum, women receive less support than in 'normal' situations, meaning that those women are less activated to RTW. Finally, the role of supervisors as case-managers for this group of employees is less well defined, especially during maternity leave.

Supervisors often serve as a case-manager in case of sick leave in The Netherlands, however, they do not play a similarly important role in supporting the employee and recognizing problems for RTW that occur during maternity leave. Most companies in The Netherlands do not have a special policy for structured contact during maternity leave. Nieuwenhuijsen et al. recommended that supervisors should communicate frequently with employees during (prolonged) sick leave and should hold follow up meetings often in order to facilitate RTW in general [14]. It seems plausible that the supervisor can play a key role in preventing work disability by acting as a case-manager and stimulating earlier contact and involvement of the OP during maternity leave.

A structural contact between supervisors and women on maternity leave, supported by early medical advice of occupational physicians during maternity leave may increase the chances of RTW after maternity leave or reduce the incidence of sick leave after maternity leave. This paper describes the design of the Mom@Work study, a randomised controlled trial (RCT) and cohort study, conducted at Body@Work, Research Centre Physical Activity, Work and Health, TNO-VUmc in Amsterdam, The Netherlands. The Mom@Work study has three aims. The first aim is to investigate the effectiveness and cost-effectiveness of an early intervention in reducing sick leave in women after maternity leave in a randomised clinical trial. Our hypothesis is that supervisors who have structural contact with their employees during maternity leave combined with occupational health care, when needed, will be more effective in reducing the number of sick leave days after maternity leave than supervisors who do not. The second aim of the study is to examine which factors contribute to RTW for women after childbirth. The third aim is to examine which factors contribute to the development of the following postpartum complaints: pregnancy-related pelvic girdle pain, depression and fatigue. The second and third aim are examined in the cohort study.

## Methods/design

### Study design

The study is designed as a simultaneous randomised controlled trial (RCT), to assess effectiveness and cost-effectiveness of the intervention in reducing postpartum sick leave, and a cohort study, to assess incidence and determinants who contribute to postpartum RTW and to the development of postpartum health complaints. The Medical Ethics Committee of VU University Medical Centre at Amsterdam, The Netherlands approved the study design, study protocol, and informed consent procedure. All participants must provide a written informed consent.

### Recruitment of companies

For practical reasons, large companies with a predominantly female workforce were preferred to enter the study. It has been estimated that annually about five percent of the women becomes pregnant in The Netherlands. Van Beukering (2002) found that health care companies had higher sick leave rates before and after maternity leave than other companies. Therefore, health care companies were over sampled in the study.

Ninety-three companies were approached and ultimately 15 companies consented to participate in the study. The participating companies included university hospitals (n = 3), child care companies (n = 3), regional hospitals (n = 2), a health care group including a regional hospital, elderly care and home care (n = 1), a ministry of the Dutch government (n = 1), a chain of supermarkets (n = 1), a youth health care company (n = 1), an occupational health service provider (n = 1), a chain of special travel shops (n = 1) and a chain of pharmacists (n = 1). The company size ranged between 391 and 52,481 employees.

### Recruitment of study population

All pregnant women who were working between January 1, 2004 and March 31, 2006 at one of the 15 participating companies in The Netherlands were able to participate in the Mom@Work study. When a woman submitted the request for maternity leave, a human resources (HR) staff member of the participating company sent a short information letter about the study, a study leaflet, two response cards and a postal envelope to this woman. If the woman was interested in participating, she was asked to complete the 'Yes' response card and mail it to the research staff. The 'Yes' response card contained screening questions for both the RCT and cohort.

#### Inclusion and exclusion criteria cohort study

Pregnant women were eligible to enter the cohort study when they met the following inclusion criteria: age between 18 and 45 years; employment for a minimum of 12 hours a week before maternity leave and intention to RTW after maternity leave. Furthermore, they had to give written informed consent and be sufficiently fluent in the Dutch language. Women were not admitted to the RCT or cohort study if they met any of the following exclusion criteria: definitely not returning to work after maternity leave; miscarriage or delivery before 27 weeks; receiving a full disability benefit; or submitting an application for a full disability benefit.

#### Specific inclusion and exclusion criteria RCT

The inclusion criteria for the RCT were stricter than for the cohort study. Women could only enter the RCT if they met the criteria of the cohort study and the following inclusion criteria: employment for a minimum of 12 hours a week until six months after the delivery and working for the same employer before and after maternity leave.

The specific exclusion criteria for the RCT were: a delivery before thirty-four weeks; return to the same employer after maternity leave is uncertain; and definitely not returning to the same employer after maternity leave. All participants of the RCT took also part in the cohort study. Women, who were not admitted to the RCT, could enter the cohort study if they met the inclusion criteria of the cohort study. Figure 1 shows an overview of the inclusion and exclusion criteria for the RCT and cohort study.

**Figure 1 F1:**
[figure not shown]
**Inclusion and exclusion criteria RCT and cohort study**. * Specific inclusion criteria RCT.

### Group allocation

Due to the fact that most supervisors managed a team of employees, the possibility existed that more than one employee would participate in the Mom@Work study. Thus, randomisation took place at the level of the supervisor rather than the participating woman. For each participating company, a randomisation list was computer-generated by an independent statistician. Because it was not known how many employees of each company would be participating in the study and some companies had a small number of employees, random allocation in blocks of four was chosen. Each block contained two intervention and two control group allocations in a random sequence. The details of the randomisation were printed on tickets and sealed into envelopes. The outside of the envelope was marked with the company's number and a number indicating the rang order. Supervisors were randomised when the participant was 35 weeks pregnant. When the researcher was informed in time that the participant gave birth before 34 weeks, the participant was not randomised, but still included in the cohort study.

Each week during the enrolment period, a list of supervisors who were to be randomised, was printed. The researcher allocated the supervisors of the women to the intervention group or to the control group by opening the next numbered envelope. The research assistant was responsible for sending emails and information to the supervisors who were randomised into the intervention group. The supervisors who were randomised into the control group did not receive any information and were not informed that their employee was participating in the study.

### Treatment groups for the RCT

#### Intervention group

The intervention concerns a minimal intervention strategy. The participant receives a phone call from her supervisor six weeks after childbirth and, if needed, support of the occupational health service providers (OHSP). The aim of the intervention is to prevent sick leave by only one phone call and by instigating earlier help by OHSP for the health problems. When health problems are pointed out during the phone call from the supervisor, the women can receive support of the OHSP at least five to seven weeks earlier than usual.

During the structured telephone contact the supervisor uses a standardised interview in the form of a checklist, and asks questions about the women's well being, the child's well being, child care, breast feeding, anticipated work problems, and the expectation of returning to work after maternity leave. When a woman expects that she is not returning to work after maternity leave, or has doubts about it, she is offered support of the OHSP by the supervisor. Only when she wants this support, the OHSP is called in. If requested by the participant, another representative of the company such as another supervisor, executive, line-manager, head of department or HR-advisor initiates this contact.

When a woman does not anticipate any problem with RTW, the supervisor does not offer further support, and he or she only asks when the woman will start working again. Women who do not expect any problem and who do not receive any early help of the OHSP, but who ultimately delay returning to work after maternity leave due to illness, receive the usual sick leave care.

If indicated during the phone call, the supervisor, participant or research team calls the OHSP that the woman needs their support on behalf of the study. A regular, but accelerated procedure for sick leave is initiated by the OHSP. In most cases, an appointment for early medical advice of the occupational physician with the participant is made within one week, instead of the usual six. The OP follows an OHSP complaint specific protocol, if available.

The supervisors receive a thorough instruction to carry out the structural contact. First, they receive an email to check if they are actually the supervisor of the participant and to check their personal data like work address and phone number. Next, they receive an information package. This package contains a study leaflet explaining the background of the study and instructions on when and how to perform the structured interview with the participant. An instruction card and checklist for this interview are also included. Then, they receive an instruction phone call from the research team four weeks after delivery. Finally, an email is sent to respective supervisors six weeks after delivery as a reminder for the phone-call. The supervisors are asked to perform the structured interview and to complete the accompanying checklist in the sixth week after delivery. They are requested to return the checklist by fax or email to the research team thereafter as soon as possible. If the checklist is not received at seven weeks after delivery, a reminder is sent by e-mail or made by telephone.

In the intervention group, supervisors are free to give their usual attention to employees who gave birth such as making home visits, calls or sending cards. If available, the policy of the company for pregnant employees or new mothers is allowed to be carried out during the study. For example, bringing a visit to the new mother with the "company's' bear" several weeks after childbirth.

#### Control group

Supervisors in the control group perform their common practice of acknowledging the arrival of their employees' newborn, for example, by making a home visit, calling or sending cards. If the participant is not able to RTW after maternity leave has ended, the standard sick-listing procedure is followed. If participants experience medical complaints during maternity leave, there is always the regular possibility of calling their supervisor or OHSP. Some OP's have reported before the start of the study that they routinely ask employees to contact them a few weeks before the end of maternity leave, in case of serious complaints during pregnancy.

### Blinding

Given the nature of the intervention, only the control group supervisors and participants are blinded to the intervention. The intervention group supervisors and participants cannot be blinded for the allocated treatment. Furthermore, the researcher and research assistant cannot be blinded for the allocated treatment. However, the data entry assistants are blinded for the allocated treatment. Data on sick leave and RTW are extracted from the routine databases of the company or the OHSP, thus, blinding does not play a role. The data will be blinded for the performance of the analysis. To guarantee blinding of the data for the analysis the participants, supervisors and companies are coded.

### Outcome assessment

All measurements, except sick leave data of OHSP or company, are performed by questionnaires. The baseline measurement consists of two parts: The first part (T0) when the employee makes herself known as participant; and the second part at 30 weeks pregnancy (T1). There is a one-year follow-up with assessments at six weeks (T2), 12 weeks (T3), 24 weeks (T4) and 52 weeks (T5) after the delivery date.

Units of health care use and productivity loss which are used to calculate costs are measured at six weeks (except work performance), 12 weeks (except work performance), 18 weeks, 24 weeks and 52 weeks after the delivery date. If a woman takes sick leave, has health care costs or has decreased work performance at 24 weeks, she receives a questionnaire on units of health care use and productivity loss again at 30 weeks, and if indicated by the same criteria also at 36, 42 and 48 weeks after the delivery date. Self-reported sick leave is assessed as part of the cost measurements, and objective sick leave data is obtained from the databases of the OHSP and, if available, from the databases of the company.

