#### RCT secondary outcome measures

In addition, data will be collected on the following items:

1. Costs are assessed from a societal perspective. Units of direct health care utilisation, both within and outside the health care sector, as well as productivity loss due to absenteeism and presenteeism are collected by cost diaries. Examples of direct health care units within the health care sector include consultations with the general practitioner, hospitalisations, and medications, and examples of direct health care units outside the health care sector include over-the-counter medication, informal care, and consultations with alternative health professionals. Costs will be calculated by multiplying the volume of resource use by cost prices, following the Dutch guidelines for economic evaluations in health care to estimate costs [15].

2. Health is measured with the RAND-36, a Dutch translation of the 36-Item Short Form Health Survey (SF-36) [16,17] and the EuroQol. The RAND-36 is a set of generic, coherent, and easily administered quality-of-life measures. It taps eight health concepts: physical functioning, bodily pain, role limitations due to physical health problems, role limitations due to personal or emotional problems, emotional well-being, social functioning, energy/fatigue and general health perceptions. It also includes a single item that provides an indication of perceived change in health. The Dutch version has a good reliability, good validity and is sensitive for changes [18]. Moreover, quality of life is also assessed with the EQ-5D also known as EuroQol (T2-T5) [19].

3. Satisfaction with the intervention is measured with the question, "Are you satisfied with the contact 6 weeks after delivery?", which can be answered on a six-point Likert scale. This question will be asked at 12 weeks after delivery.

4. Self-reported feelings of recovery from complaints, also called global perceived effect (GPE) is measured with the question, "To what extent have your complaints changed since 6 weeks after the delivery?", which can be answered on a seven-point Likert scale, with a range from "1" (completely recovered) to "7" (worse than ever). Again, this question will be asked at 12 weeks after delivery.

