### Analysis

For the RCT, data will be analysed using statistical tests such as linear regression analysis and Cox regression analysis. The dependency of the observations will be taken into account by performing a multilevel analysis. The multilevel analysis will be performed with a four-level data structure where time, participants, supervisors and companies will be defined as levels 1, 2, 3 and 4, respectively. The analyses will be adjusted for baseline and prognostic dissimilarities, if necessary. Both an intention-to-treat analysis and a per-protocol analysis will be performed. For the cohort study, multilevel analysis will be performed with a three-level data structure where time will be defined as level 1; participants, level 2; and the companies, level 3.

The economic evaluation, which will be performed from a societal perspective, will consist of an analysis of differences in the total, direct and productivity loss costs between the intervention and control group, as well as a cost-effectiveness and cost-utility analysis of the intervention compared to common practice. In the cost-effectiveness analysis, sick leave will be the effect measure and the total costs will comprise all costs except those of productivity loss. Utilities will be based on the Euroqol questionnaire [19]. Quality Adjusted Life Years (QALY) will be calculated by multiplying the utility with the amount of time a patient spends in this particular health state. Incremental costs per QALY gained will be calculated applying both Dutch and UK tariffs. Bootstrapping methods will be used to estimate 95% confidence intervals for the incremental cost-effectiveness ratios and to derive cost-effectiveness planes and acceptability curves.

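### Cost questionnaires at 30 to 48 weeks depend on each woman's own sick leave, costs or work performance after randomisation, which can bias the cost comparison if that status differs by arm

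*Protocol article*

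**What the plan says.** The section Outcome assessment fixes the cost schedule. Every woman is measured at six weeks, then at "12 weeks (except work performance), 18 weeks, 24 weeks and 52 weeks after the delivery date"; work performance is left out at the first two times. After 24 weeks the schedule becomes conditional. The entry rule for the 30-week form is "If a woman takes sick leave, has health care costs or has decreased work performance at 24 weeks", and the later forms follow "and if indicated by the same criteria also at 36, 42 and 48 weeks after the delivery date".

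The same section names a second source for one component only: "objective sick leave data is obtained from the databases of the OHSP and, if available, from the databases of the company". It states that everything else is measured by questionnaire.

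Under RCT secondary outcome measures, costs cover health care inside and outside the health care sector, including over-the-counter medication and informal care, "as well as productivity loss due to absenteeism and presenteeism are collected by cost diaries". The section Analysis plans "an analysis of differences in the total, direct and productivity loss costs between the intervention and control group", plus a cost-effectiveness and a cost-utility analysis. In the cost-effectiveness analysis, productivity loss is excluded from the costs and sick leave is the effect measure.

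**The concern.** Supervisors are randomised at 35 weeks of pregnancy, and the trigger is read at 24 weeks postpartum or later. It is therefore a post-randomisation variable, and one of its three components, sick leave, is what the intervention is designed to reduce. A woman who is negative at 24 weeks, or who turns negative at a later form, receives nothing more until 52 weeks, even if she then uses care or works below capacity. If the arms differ in the share of women who meet the trigger, they also differ in how completely later costs are recorded. Randomisation does not protect against this. Bootstrapping, the method named for uncertainty, deals with sampling error and not with unequal ascertainment.

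Cost-effectiveness is part of the trial's first aim. Its cost side rests on health care use and informal care, for which no source other than these forms is named.

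**Working it through.** The article gives no figure on this point, so there is none to reproduce. The check has three parts.

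**1. Which outcomes depend on the conditional forms**

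- Health care use, informal care and presenteeism: questionnaire only, so exposed.
- Absenteeism: also in the occupational health service databases and, where available, company databases. The primary sick leave and return-to-work outcomes, and sick leave as effect measure, can be taken from there.
- EQ-5D utilities: collected from all women at 6, 12, 24 and 52 weeks (T2 to T5). The cost-utility analysis is exposed only through its costs.

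**2. If the 52-week form looks back to the last form received**

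The recall length at 52 weeks is then 52 minus the week of the last form:

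- last form at 24 weeks: 52 − 24 = 28 weeks
- at 30, 36 or 42 weeks: 22, 16 or 10 weeks
- at 48 weeks: 52 − 48 = 4 weeks

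No period is lost, but recall still ranges from about 4 to 28 weeks according to outcome status.

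**3. If the 52-week form does not look back (illustration on assumed inputs)**

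Let p be the share of women positive at 24 weeks, s the chance that a positive woman is positive again in the next six-week window, and r the chance that a negative woman becomes positive. Take s and r as equal in both arms, give every positive window the same cost, count unsent forms as zero, and send each form only after a positive previous form.

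- True positive windows at 30 to 48 weeks: update p to p·s + (1 − p)·r four times and add the results.
- Recorded positive windows: p·(s + s² + s³ + s⁴).

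Worked case: p = 0.30 (control) and 0.20 (intervention), s = 0.5, r = 0.10. These values of p are borrowed from the sick leave rates under Sample size, which refer to the end of maternity leave and not to this trigger.

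- Control, true: 0.220 + 0.188 + 0.175 + 0.170 = 0.753. Recorded: 0.30 × 0.9375 = 0.281, or 37%.
- Intervention, true: 0.180 + 0.172 + 0.169 + 0.168 = 0.688 (from unrounded terms). Recorded: 0.20 × 0.9375 = 0.188, or 27%.
- Difference, true 0.065, recorded 0.094; ratio 1.44.

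| r | s | Captured, control | Captured, intervention | Recorded / true difference |
|---|---|---|---|---|
| 0.05 | 0.5 | 53% | 42% | 1.19 |
| 0.05 | 0.8 | 70% | 59% | 1.15 |
| 0.10 | 0.5 | 37% | 27% | 1.44 |
| 0.10 | 0.8 | 56% | 43% | 1.33 |
| 0.20 | 0.5 | 24% | 17% | 2.21 |
| 0.20 | 0.8 | 41% | 29% | 1.81 |

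Both differences are proportional to the arm difference in p, so the ratio does not depend on the level of p. It equals the sum of s, s², s³, s⁴ divided by the sum of the same powers of (s − r); for the worked case, 0.9375 / 0.6496 = 1.44. With p at 60% against 50% the ratios are unchanged, and capture is 44–87% against 38–83%. With 30% in both arms the loss is equal and no arm difference arises. If more intervention than control women were triggered, an extra cost in the intervention arm would be inflated instead.

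**The case against.** The strongest reply is that every woman has a cost measurement at 52 weeks and that its recall period is not stated. A condensed article may fairly leave this to the full protocol. A look-back to the last form fits the schedule well and would close the gap in coverage. The mention of cost diaries also leaves open what period each instrument covers. This stands as a limit on size. It does not remove the problem, because recall length would still depend on outcome status.

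The trigger is also broad. Any health care cost counts, so many women may stay on the schedule whatever their sick leave. The intervention may also bring some women into occupational health care earlier. The direction of an arm difference in the composite at 24 weeks is thus not settled. The text further says only that the same criteria apply at 36 to 48 weeks; judging them at the preceding form is the natural reading, not a stated one.

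A reader might infer that an untriggered woman goes unobserved for most of the second half of the year. With a six-week recall at 52 weeks, weeks 24 to 46 would be lost: 22/52 = 42% of the year and 22/28 = 79% of the last 28 weeks. The article gives no such recall period. A reader might also infer that the design produces a false saving of a definite amount. That would need a difference in trigger shares, no look-back at 52 weeks and unsent periods valued at zero; the article states none of these.

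**Conclusion.** The concern holds as a conditional risk of bias in a secondary outcome. The schedule itself makes ascertainment, or at least recall length, of health care use, informal care and presenteeism between 24 and 52 weeks depend on post-randomisation outcome status. This can bias the between-arm cost comparison and the cost side of the cost-effectiveness and cost-utility analyses if trigger status differs by arm. The bias favours the intervention if the intervention lowers trigger prevalence and unsent periods are not recovered at 52 weeks.

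The size cannot be derived from the article. The factor of 1.15 to 2.21 shows only what the mechanism does under the assumptions in the working, and it applies to the 30–48 week window alone. Database sick leave and return-to-work outcomes and EQ-5D utilities are untouched.

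**What to change.** Send the short cost and productivity questionnaire to all women in the RCT at 30, 36, 42 and 48 weeks, regardless of earlier answers. This removes the dependence on outcome. It costs extra mailings and some respondent burden.

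If the conditional schedule is kept, have the 52-week form ask every woman about the same period since 24 weeks, and base the arm comparison on that common measure. The price is a recall of 28 weeks for everyone.

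In either case, do not count unsent periods as zero. Imputation alone is not an adequate remedy: no untriggered woman is observed in the window, so a model would have to extrapolate from earlier forms or from triggered women. Tabulating by arm how many women were sent each form costs nothing and would show whether trigger status differs.
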